**Methods:**

This study is a cluster randomized controlled trial (CRCT). A total of 285 older adults (age ≥ 60) from twenty elderly centres as clusters will be randomly selected and assigned to intervention groups (IGs, *n* = 16) or control groups (CGs, *n* = 4). Each IG will be randomly assigned to one of the four combinations of three training modes that include cognitive (A), physical (B), and combined cognitive and physical training (CCPT, i.e. C), namely Mixed ABC, A + B, C + A, B + C. The intervention will last for 4 months in which the training is conducted for 16 sessions, 2 sessions per week, and 60 min per session. Four repeated assessments (pre-test, two post-training tests after 2 months and 4 months, and a follow-up test) will be conducted. The CG will only receive the four repeated assessments but no intervention. The outcome measures include cognitive tests (tests of execution, memory, and psych-social status), physical fitness, and dynamic balance tests.

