## Methods

### Research design

This study is a cluster randomized controlled trial (CRCT), to be carried out in 20 community elderly centres (see Fig. 1). The elderly centres will be randomly selected from the population list of elderly service providers in the 18 districts of Hong Kong and assigned to either one of the 4 Intervention Groups (IGs) or the Control Group (CG). There will be 16 centres in the IGs and 4 centres in the CG participating in a 6-months program (4-month intervention with 2-month follow-up). The 20 participating centres will be equally allocated to two Phases, I and II, with each Phase involving 8 centres in IGs and 2 centres in CG. Each IG will be randomly assigned to one of the four combinations of three training modes that include cognitive (A), physical (B), and combined cognitive and physical training (CCPT, i.e. C), namely Mixed ABC, A + B, C + A, B + C. The intervention will last for 4 months in which the training is conducted for 16 sessions, 2 sessions per week, and 60 min per session.

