**Fig. 1 Fig1:**
[figure not shown]
Flow diagram of the study through two phases of the CRCT, including recruitment, allocation, intervention, and data collections points

In each phase, four repeated assessments (T1-T4) will be conducted: T1 is the pre-test before intervention; T2 and T3 will be conducted on intervention right after the end of 2-month and 4-month, respectively; T4 is a follow-up test conducted 2 months after the completion of all intervention training. Participants of CG will be asked to assume regular-daily habitual activities and take four repeated assessments only.

The study is designed in accordance with the SPIRIT (Standard Protocol Items: Recommendations for Interventional Trials). The study protocol has been approved by University Research Ethics Committee (REC/19–20/0066) and registered at ClinicalTrials.gov Identifier: NCT04727450.

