### Sample size

As suggested by Brown et al. (2015) [20], the first step of CRCT sample size estimation is to determine one for a non-clustered design. Based on the repeated measures of ANOVA analyses of 4 trials by 5 groupings (4 IGs + 1 CG) with parameters set to an effect size of 0.175 (small to medium), an alpha level of 0.05, power of 0.90, rho of 0.5, the sample size (*n*_*n*_) estimated is 95 (calculated by G*Power software). Next, the second step is to determine the design effect (*D*_*e*_) for clustering estimation. It is calculated with a group size of 15 and ICC of 0.1 (from previous a study titled BIGMAP, to be published) [15] and yields 2.4. The required sample size for a CRCT is 228 (i.e., *n*_*n*_×*D*_*e*_). By considering a 20% of attrition rate of the participants, the total sample size (*N*) of this study is set at 285, composed of 20 groups/centres of 14–15 participants each.

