### Interventions

Each selected elderly centre will be randomly assigned to either IGs or CG and asked to help to recruit participants with a sample size of 14–15 older adults. There will be 16 centres in the IGs to receive four combinations of three training modes (A: cognitive training only, B: physical training only, C: CCPT) and with 4 centres in IGs. The four types of combinations are 1. Mixed ABC, 2. A + B, 3. B + C, 4. C + A, matched with 4 CGs in total. For the case of combination 1. Mixed ABC, participants will receive different training modes every 2 consecutive weeks with randomized order. For the case of combinations 2, 3, and 4, the participants’ centres will receive an assigned sequential order of two training modes with each mode lasting for 2 months. All participants of IGs will attend training sessions twice a week, and 60 min duration per session (per mode). The random allocation sequence of intervention was generated by a blinded statistician external to the research team. Due to the nature of each intervention, blinding cannot be applied to the participants, while the blinded group allocation will be applied to the data assessors and analysts. Each subject will be identified by the number code. Data from those participants having more than 70% attendance will be analyzed. No further follow-up with missing cases will be done because they will be usually missing at random (such as absences due to doctor’s appointments or being sick).

The three training modes (A, B, and C) are introduced as follows:A: Cognitive training only

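### Analysing only participants with more than 70% attendance opens the intervention-versus-control comparison to selection bias

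*Protocol article*

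**What the plan says.** The rule on who is analysed is in the Interventions section of the protocol article: "Data from those participants having more than 70% attendance will be analyzed". The next sentence deals with missing data: "No further follow-up with missing cases will be done because they will be usually missing at random". The examples it gives are "such as absences due to doctor’s appointments or being sick".

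The control group has nothing to attend except the tests. The Abstract (Methods) says "The CG will only receive the four repeated assessments but no intervention", and the Research design section, in the text after Fig. 1, says "Participants of CG will be asked to assume regular-daily habitual activities and take four repeated assessments only".

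The control group nevertheless carries part of the argument. The hypothesis under Research objectives and hypothesis expects every mixed modality to do better than control, and the Statistical analysis plan section codes control as level 0 of a five-level group factor. That section names no other analysis set.

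**The concern.** Attendance is behaviour that follows randomisation and can depend on the assigned programme. Selecting on it means the analysed groups are no longer the groups that randomisation formed. If attendance means training sessions, four arms lose their poor attenders and the control arm loses nobody comparable. Regular attenders may well be healthier or more motivated, and so may fare better on cognition and fitness with or without training. Part of any difference from control could then come from the selection.

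The justification does not help. Sickness plausibly relates to the outcomes being measured, so it is a poor example of harmless missingness. Missing at random is also a statement about data that were not observed, whereas the attendance rule discards data that were. If the assumption did hold given the observed visits, a likelihood analysis of all available data could rely on it without excluding anyone. The assertion is therefore an argument against the filter.

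**Working it through.** **1. The plan's own figure.** Inputs from the Sample size section: f = 0.175, alpha 0.05, power 0.90, rho 0.5, 5 groups, 4 times, cluster size 15, ICC 0.1, attrition 20%.
- Group-by-time interaction test at N = 95: noncentrality = f² × N × m/(1 − rho) = 0.030625 × 95 × 4/0.5 = 23.3, with df 12 and 270. Power is 0.909. The smallest N is 93, which becomes 95 in five equal groups.
- Design effect = 1 + (15 − 1) × 0.1 = 2.4, and 95 × 2.4 = 228.
- 228/0.8 = 285, or 14.25 per centre.

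The stated 285 reproduces, so the sample size is not in question here. It also shows that the planned test is one of change over time.

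**2. Whom the filter can reach.**
- Attendance at sessions: only the 16 intervention centres (16 × 14.25 = 228 people). The 4 control centres (57 people) have no sessions.
- Attendance at assessments: more than 70% of four visits means at least 3 of 4, in any arm.

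**3. The denominator.** The Research design section says "The intervention will last for 4 months in which the training is conducted for 16 sessions, 2 sessions per week, and 60 min per session". Two sessions a week for about 16 weeks is about 32, not 16. More than 70% means at least 12 of 16 (threshold 11.2) or at least 23 of 32 (threshold 22.4). Someone who attends 12 to 22 sessions is in or out depending on which count applies.

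**4. Size of the possible bias, as an illustration.** Two assumptions are needed, and the document gives neither: the fraction q of intervention participants dropped (the lowest attenders), and the correlation r between attendance and favourable outcome change in the absence of any training effect. Under a normal model the spurious difference from an unfiltered control group is r × φ(z_q)/(1 − q), in SD units of the change.
- q = 20%: φ(z_q)/(1 − q) = 0.280/0.8 = 0.350
- q = 30%: φ(z_q)/(1 − q) = 0.348/0.7 = 0.497

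| q | r = 0.2 | r = 0.3 | r = 0.5 |
|---|---|---|---|
| 20% | 0.070 | 0.105 | 0.175 |
| 30% | 0.099 | 0.149 | 0.248 |

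A simulation at q = 20%, r = 0.3 gave 0.106, in agreement. At q = 10%, r = 0.1 the difference is only 0.02.

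**5. What that does to a test.** Take a two-sided 5% comparison of pooled intervention against control (a simplification, not the plan's own test), with no other losses. SE = √[2.4 × (1/(228(1 − q)) + 1/57)]. For q = 20% this is √[2.4 × (1/182.4 + 1/57)] = 0.235. With a bias of 0.105 the shift is 0.105/0.235 = 0.45 standard errors, and the false-positive rate is about 7%. Over the six cells of the table the rate runs from 6% (q = 20%, r = 0.2) to 18% (q = 30%, r = 0.5).

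**6. Scale.** These SD differences cannot be set beside f = 0.175. If only control differs among five equal groups, f = d × √(0.2 × 0.8) = 0.4d, so f = 0.175 is about 0.44 SD. Conversely, 0.07 to 0.25 SD is f of about 0.03 to 0.10.

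**The case against.** Attendance is undefined, and the sentence on missing cases is not confined to the intervention groups. A reader might infer that the filter certainly acts on the intervention arms alone and leaves control whole. The document does not establish that: the word could cover assessments, and control participants who miss visits get no further follow-up either. Session attendance remains the natural sense in the Interventions section, and the other sense is still selection after randomisation.

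The planned test concerns change. If attendance tracked only a stable level of ability, T1 would shift together with T2 to T4 and the group-by-time interaction would be unaffected. This stands: bias in that test needs a link with change, which is how r is defined above. A group main effect would be exposed to level as well.

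The Statistical analysis plan section puts its main focus on differences among the intervention groups, where one threshold applies to all. That lessens the exposure there without removing it. Board games, line dancing and combined training could draw different attendance, but the document does not say that they will.

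The sentence on follow-up may mean only that missed sessions or tests are not made up. The examples are single absences, and nothing says that poor attenders stop being assessed. It should be clarified and not read as a decision to stop assessing them.

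Finally, a separate statistical analysis plan may add an analysis of everyone as assigned. Its absence from this article is not the point made here; the point is the rule that the article does state.

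**Conclusion.** The concern holds in this form: the only analysis set the article states selects on attendance after randomisation, without a per-protocol label, and the comparison with control is open to selection bias as a result. Comparisons among the intervention groups are open to it only if attendance differs by mode. *Open to* is as far as the document goes. Size and direction depend on q and r, and it gives neither. Under the illustrative values the spurious difference is 0.07 to 0.17 SD at q = 20% and 0.10 to 0.25 SD at q = 30%. At q = 20% and r = 0.2 to 0.3 the effect on the error rate is modest (6% to 7% instead of 5%); the 18% belongs to the extreme corner.

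Two stronger readings should be resisted. One is that the bias is as large as the planned effect because 0.17 SD resembles f = 0.175; the scales differ. The other is that the filter must bring the analysed number below 228. The sample size was inflated with the words "By considering a 20% of attrition rate of the participants", and attrition is not defined there, so poor attenders may already be counted in the 20%. A shortfall arises only if all losses together exceed that allowance.

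**What to change.** - Make the primary analysis include all participants in the arm of their centre, whatever their attendance.
- State that the already scheduled T2 to T4 assessments are offered to everyone, including poor attenders and those who stop training.
- State that the mixed model is fitted by likelihood to all available visits.
- Keep the set with more than 70% attendance as a labelled per-protocol sensitivity analysis. Define attendance (sessions or assessments) and its denominator, and reconcile the 16 sessions with two per week over four months.
- Drop the missing-at-random assertion as a reason for excluding anyone.

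The cost is a change of wording and the completion of assessments that are already scheduled. The estimated effect may be slightly smaller. N does not change, since 285 already carries the 20% allowance.

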### Outcome measures

Participants will take part in evaluation for four times, including a pre-test (T1), two post-tests (T2 and T3) at 2-month intervals, and a follow-up test (T4) two months after the intervention. The evaluators will be blind to the group membership of participants. Each evaluation includes three aspects of testing that are cognitive tests (60 min), fitness tests (30 min), and mental-related surveys (15-20 min). The total testing time per participant is less than 2 h.

#### Primary outcome: cognitive measures

The main cognitive outcome measures will target executive functions which involve a variety of higher-order cognitive processes, such as cognitive flexibility, planning, decision making, attention, and memory. Three tests, Wisconsin Card Sorting Test-computer version (WCST), Color Trial Test (CTT), and Rivermead Behavioral Memory Test (RBMT) will be used as the cognitive outcome measures. These tests are chosen based on their relevance to the BIGMAP contents which were mainly designed to train cognition in terms of executive functions and memory, and physical functions. These well-established tests with proven validity and reliability are all commonly used in studies testing cognitive functions [20, 23–25], and all the tests have been translated into Chinese used in Hong Kong. Details of test descriptions are listed as follow:

The WCST is one well-known measure of executive functions, which involves mainly the assessment of abilities related to shifting cognitive strategies and abstract reasoning in response to environmental contingencies [26]. Before testing, color blindness needs to be excluded so that it does not influence the test result [27]. A computer version of WCST with 128 cards will be used in this study [28]. The participants will be required to sort two sets of 64 responses cards to match either number (one, two, three, and four), form (circles, crosses, stars, and triangles), or color (red, yellow, green, and blue), which will discreetly and periodically change during the course of sorting without the participants being informed. The participants have to shift sets accordingly and sort cards following the new sorting rule in a computer. Set shifting difficulties will be indicated by preservative errors; thus, higher scores on this test represent worse performance [29, 30]. The WCST is scored according to nine categories and will be automatically summarized in a result sheet provided by the computer. It takes approximately 30 min per participant to complete this test.

The Chinese CTT will be selected to assess the sustained attention and divided attention of the participants as it requires cognitive flexibility and visuomotor skills to complete the task. The CTT is not a language biased test but relies on the use of numbered, colored circles and sign language symbols, thus it is suitable for elderly participants no matter whether they can read English alphabet letters or Chinese characters. The CTT is comprised of two parts: (a) CTT1 is administered first and requires the participant to connect 25 number circles, which are randomly located on a sheet of paper, in an ascending numbered sequence (1 to 25); (b) In CTT2, the participant is required to connect number circles from 1 to 25 while alternating between two colors—pink and yellow. In this study, the time-related indices, such as Time of CTT1 and CTT2 (in seconds), CTT2-1 time difference, etc. will be recorded and used for statistical analysis [31, 32].

The Chinese RBMT will be used for the assessment of participants’ memory in this study [33]. It consists of 11 subtests that cover the aspects of visual, verbal, recall, recognition, immediate, and delayed every memory. Additionally, prospective memory skills and the ability to learn new information are also measured. It will take around 30 min to complete the testing. Raw scores of the 11 subtests will be converted into subtest scaled scores. The sum of 11 scaled scores will be recorded. In addition, a General Memory Index (GMI), representing overall memory performance is also created based on the sum of scaled scores and a conversion table. From the conversion tables, the confidence intervals and percentile ranks for each GMI will be also reported [34].

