### Statistical analysis plan

Data analysis will be performed using the Statistical Package for social sciences (IBM SPSS ver. 27). All data points that were considered outliers, which are out of the interquartile range (IQR) covering the 50% central of samples, will be excluded from analyses. For analyzing program effects, a mixed-effects ANOVA will be used. In this model, there will be a between-subjects factor consisting of five groups (CGs = 0, IGs = 1 to 4) and a within-subject factor consisting of four Trials (Time = 1 to 4). The dependent variables will be the outcome measures of the three cognitive tests and the five physical fitness tests. The independent variables will be time (1 pre-test, 2 post-tests, and 1 follow-up) and intervention (IGs with 4 combinations of training modes & CGs). The participating elderly centre as a cluster will be treated as a random effect. Assumptions (normality, sphericity, etc.) for mixed-effects ANOVA will be tested using an alpha level set as 0.05. The focus of this mixed-effects ANOVA will be mainly on the between-group differences, i.e., the differences among the four IGs. Post-hoc comparisons among IGs will be conducted with Bonferroni correction after finding significant effects. Next, for analyzing specific intervention effects in the 3 treatments crossover design, a similar mixed-effects ANOVA will be used. In this second model, there will be one within-subject factor of four repeated trials (Time = 1 to 4). The dependent variables will be the outcome measures of the three cognitive tests and the four physical fitness tests. The independent variables of time (pre-test, 2 post-tests, and follow-up) and three training modes will be examined by ANOVA with repeated measures. The focus of the second model is to examine the individual effect of the three training modes, so a pre-planned contrast will be conducted to examine their effects. Based on these statistical analyses, results and conclusions will be drawn.

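### The primary outcome is three multi-score cognitive tests with no designated score and no stated error control across scores, so the primary false-positive rate is about 13–14% at best-case counting and could approach 50%

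*Protocol article*

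**What the plan says.** All of this is in the Methods of the protocol article.

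- **Primary outcome: cognitive measures.** The section states: "Three tests, Wisconsin Card Sorting Test-computer version (WCST), Color Trial Test (CTT), and Rivermead Behavioral Memory Test (RBMT) will be used as the cognitive outcome". The tests are not ranked.
- **WCST.** "The WCST is scored according to nine categories and will be automatically summarized in a result sheet provided by the computer". One index is linked to a construct: "Set shifting difficulties will be indicated by preservative errors; thus, higher scores on this test represent worse performance" (evidently perseverative errors).
- **CTT.** Three time indices are named and the list then ends in *etc.*: "the time-related indices, such as Time of CTT1 and CTT2 (in seconds), CTT2-1 time difference, etc. will be recorded and used for statistical analysis".
- **RBMT.** "The sum of 11 scaled scores will be recorded". There is also a General Memory Index (GMI), "representing overall memory performance is also created based on the sum of scaled scores and a conversion table".
- **Statistical analysis plan.** The dependent variables of the first model (five groups by four time points) are the outcome measures of the three cognitive tests, plus five fitness tests. No score is selected within a test. A second model takes the cognitive measures again to look at the three training modes. The one multiplicity provision is this: "Post-hoc comparisons among IGs will be conducted with Bonferroni correction after finding significant effects".
- **Sample size.** Alpha 0.05 and power 0.90 are set for one generic repeated-measures ANOVA. In the analysis section itself, 0.05 is attached only to the checks of model assumptions.

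**The concern.** A primary outcome should tell the reader, before the data are seen, which result will carry the conclusion. Here it is a family of scores, and one member list is explicitly unfinished. The stated Bonferroni step deals with a different family: pairs of intervention groups within one outcome, after that outcome has shown an effect. It does nothing about the number of outcomes tested.

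The stated hypothesis does not narrow the choice, because it speaks only of higher cognition and fitness scores in general. At stake is whether a claim that mixed training improves cognition is confirmatory, or is the most favourable of several scores.

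**Working it through.** **1. The plan's own figure.** Inputs from the Sample size section: f = 0.175, alpha 0.05, power 0.90, rho 0.5, 5 groups, 4 time points, cluster size 15, ICC 0.1, attrition 20%. The group-by-time interaction test has noncentrality λ = f²·N·m/(1−rho), with 12 and 3(N−5) degrees of freedom.
- At N = 95: λ = 0.030625 × 95 × 4 / 0.5 = 23.275 and power is 0.909. The minimum N is 93, or 95 when rounded up to five equal groups.
- Design effect 1 + 14 × 0.1 = 2.4; 95 × 2.4 = 228; 228 / 0.8 = 285.

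The plan's 285 is reproduced. It is sized for one test at 0.05.

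**2. Scores listed under the primary outcome.** WCST 9, CTT 3 (plus whatever *etc.* adds), RBMT 2: 9 + 3 + 2 = 14. Two of these are derived: the CTT2-1 difference from CTT1 and CTT2, and the GMI from the RBMT sum.

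**3. Chance of at least one false positive when no programme works.** Assumptions: each score is tested at 0.05 without adjustment. The documents give no correlation between scores, so a range is shown. For independent scores the formula is 1 − 0.95^k:
- k = 3: 1 − 0.95³ = 0.143
- k = 14: 1 − 0.95¹⁴ = 0.512

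For equally correlated scores, by simulation (ranges cover 1-df and 12-df tests):

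| Correlation | One score per test (3) | All 14 listed scores |
|---|---|---|
| 0 | 14% | 51% |
| 0.3 | 14% | 44–46% |
| 0.5 | 13% | 35–38% |
| 0.7 | 11–12% | 25–28% |
| 0.9 | 8–9% | 14–15% |

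**4. Allowing for the derived scores.** Here the GMI is set identical to the RBMT sum and CTT2-1 is computed from CTT1 and CTT2. The assumed correlations are 0.6 between CTT1 and CTT2 and 0.1 to 0.3 between tests. The 14-score figure is then 42–45%, 37–41%, 32–35% and 26–28% for a correlation among WCST scores of 0.3, 0.5, 0.7 and 0.9.

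**5. After the fix.** Three named scores under Holm: at most 5% overall. The steps are 0.05/3 = 0.0167, then 0.025, then 0.05. With the inputs of step 1 and N = 95, power for a single score is 0.909 at 0.05, 0.853 at 0.025 and 0.815 at 0.0167.

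**The case against.** The strongest reply is that this is a condensed article and a separate analysis plan may choose the scores and handle multiplicity. That holds for detail the article leaves out. It does not cover what the article does fix: an open list inside the primary outcome, an analysis section that enters the measures of all three tests, and a correction aimed only at group pairs.

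A reader might also infer more than the documents support. Four limits stand:

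- **That success means a significant result on any one score.** No such rule is written. No success rule is written at all, which permits that reading without stating it.
- **That each score is tested at 0.05.** This is a reasonable inference from the sample size, not a statement in the plan.
- **That all nine WCST categories are analysed.** The text describes what the computer reports, and the same paragraph singles out one index. Only the CTT indices are expressly said to go into the analysis, and only the CTT list is open.
- **That the false-positive rate is 35–50%.** This needs all 14 scores, no adjustment and correlations of roughly 0 to 0.5. The 51% end needs independence, which cannot hold exactly when two scores are computed from others.

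It is also fair to say that the remedy is not free. Power at the first Holm step falls below the planned 0.90.

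**Conclusion.** The concern holds in a conditional form. As written, the plan designates no primary score, leaves the CTT list open and states no error control across the scores and tests that make up the primary outcome.

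The size depends on how many scores are tested. On the most favourable count, one score per test, the primary false-positive rate is about 13–14% at correlations of 0 to 0.5, more than twice the nominal 5%. If all 14 listed scores were tested it would be up to about 50%, falling to roughly 14% if they were correlated at 0.9. Indices added under *etc.*, or counting the second model's re-tests as primary, would raise these figures. All of them assume unadjusted tests at 0.05 and no true effect.

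The documents do not support a single figure of 35–50%, nor the statement that the trial will declare success on any score.

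**What to change.** Before any outcome is analysed by arm:

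1. Delete *etc.* from the CTT description so that the list is closed.
2. Name one primary score per test. For example: WCST perseverative errors, which the protocol itself singles out; one named CTT time index; and the RBMT GMI. The sponsor may prefer other scores; what matters is that they are fixed in advance.
3. Test the three with Holm at an overall 0.05 in the first, five-group model. Keep the existing Bonferroni step for group pairs within an outcome.
4. Label the remaining WCST, CTT and RBMT indices, and the second model's re-tests of cognition, as secondary or exploratory.

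**Cost.** Steps 1 to 4 change wording only; no data collection changes. The statistical cost is power at the first Holm step (0.0167), about 0.81 against 0.91 at 0.05 for a single score under the plan's own inputs; the later steps soften this. The stated 0.90 should therefore be described as power per outcome at 0.05. No added enrolment is proposed.
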